## Abstract

(1) Background: Type 1 diabetes is a chronic disease that creates a high demand and responsibility for patient self-care. Patient education, self-care training and the management of derived complications are great challenges for nurses. The objective of this project is to evaluate the efficacy of a therapeutic education program for type 1 diabetes. (2) Methods: Participants recruited to the study will be adult patients with diagnosed type 1 diabetes attending the clinic at the study site. A nurse diabetes educator will deliver a four-session education program. A two-group randomized controlled trial will be used in this study, with an intervention group and a control group. The subjects included in the experimental group will attend some health education sessions, while control group participants will receive the existing standard care provided by the endocrinology and nutrition unit of the hospital. Measurements and evaluations will be conducted at the baseline prior to the intervention and at 1 and 3 months from the intervention. (3) Conclusions: The primary outcome is improving patients’ knowledge about diet and treatment management. Secondary outcomes are improving patients’ glycemic control and mood. The findings from this study will help to determine the effect of diabetes education about self-care and treatment in patients with diabetes, as well as helping to decrease short-term and long-term complications and reduce health care costs.

## 1. Introduction

Type 1 diabetes is an autoimmune disease affecting 1 in every 300 persons, and the number of newly diagnosed cases is growing [1]. The number of people living with diabetes is expected to continue to increase, affecting an estimated 550 million by 2030. Diabetes is a prominent public health concern associated with increased premature mortality [2]. Long-term microvascular and macrovascular complications in patients with type 1 diabetes have been shown to be reduced with optimal glucose control [3]. In addition to pharmacological treatment, the importance of lifestyle modification, mainly diet, has been demonstrated [4]. Evidence has suggested that diabetes self-management education improves short-term glycemic control and reduces diabetes complications. Practice nurses are in a good position to provide monitoring, tailored feedback and health education [5]. 

The American Diabetes Association 2015 *Standards of Medical Care in Diabetes* recognizes diabetes self-management education (DSME) as a holistic aspect of the care of people with this chronic pathology [6,7]. Diabetes self-management education is defined as a continued facilitation of the development of the knowledge and abilities necessary for the optimal self-management of diabetes [8]. Evidence suggests that DSME is cost-effective [9] and associated with favorable changes in knowledge, clinical outcomes, self-efficacy and other psychosocial outcomes, screening for complications, risk factors for cardiovascular events and quality of life [10,11,12].

The recommended treatment regimen for type 1 diabetes is complex, and it requires the frequent monitoring of blood glucose levels, the control of carbohydrate intake, frequent insulin administration and participating in moderate-intensity physical activity [6]. Type 1 diabetes is a chronic disease that creates a high demand and responsibility for patient self-care. Patient education, self-care training and the management of derived complications are great challenges for nurses [13].

Four or more capillary blood glucose tests are required daily to safely and effectively adjust insulin doses. It is often difficult to perform the necessary daily check-ups due to pain from the finger-stick. Over time, patients develop calluses on their fingertips due to numerous punctures [14]. Owing to the progression of technology, in recent years sensors have been created that allow glucose monitoring, such as the FreeStyle Libre (FSLCGM Abbott Diabetes Care, Alameda, CA, USA). This rapid glucose monitoring system provides the mechanical reading and continuous measurement of interstitial fluid glucose concentration and provides the corresponding ambulatory glucose profile. Patients can scan their sensor with a reader or with their personal mobile device through an application. They can meet target glucose levels and average periods of hypoglycemia and hyperglycemia, as well as set alarms to notify them of high or low blood glucose levels [15,16].

This paper describes a study protocol for analyzing the influence of therapeutic education in the treatment management and self-care of patients with type I diabetes. To assess whether education influences glucose control, we will review the records of the continuous glucose monitoring sensor. We will compare the sensor parameters before and after the educational intervention, such as time in the optimal glycemic range, time in hypoglycemia or hyperglycemia and average glucose level. A pre-/post-intervention test of knowledge on the management of the disease will be administered to assess the knowledge acquired after the therapeutic education. Finally, we will analyze whether the change in the level of knowledge and in glycemic control influences or has any repercussions for the emotional state of the patient.

## 2. Materials and Methods

### 2.1. Design

There will be two groups in this randomized controlled trial project, an intervention group and a control group. Patients included in the intervention group will participate in four sessions of therapeutic education on the management of diabetes, while the subjects included in the control group will have access to the standard care provided by the endocrinology and nutrition unit of the hospital. The administration of tests and questionnaires as well as the evaluation of the glycemic record will be conducted at the baseline and at 1 and 3 months from the intervention. 

### 2.2. Population and Sample

This study is aimed at patients who came to the endocrinology and nutrition unit with a diagnosis of type 1 diabetes mellitus. Participants will be recruited during an endocrinology consultation with a medical professional specializing in diabetes. They will be recruited through random sampling at a public hospital in Spain. 

Randomization in blocks of 10 will be used (five experimental and five controls) to achieve balance in the randomization procedure. A person unrelated to the research objectives and data collection will prepare the sealed envelopes according to the generated randomization list. A unique patient ID will be assigned, and each patient will be allocated into one of the two groups. 

The sample size will be calculated based on Cohen’s (1992) recommendation for the expected differences between groups. Previous studies that examined the effect of diabetes self-management education on glycemic control and health-related self-care in patients with diabetes suggested a medium effect size. Given the medium effect size (0.5), a repeated-measures analysis of covariance will be performed to test for differences between the two groups, and approximately 176 participants will be required to achieve a 95% power at a 5% level of significance [17].

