### 2.4. Intervention

#### 2.4.1. Diabetes Education Program

Participants randomized to the intervention group will receive a structured program of therapeutic education organized over four consecutive days. The organization of the sessions is shown in Figure 1. 

The therapeutic education will be provided by an advanced practice nurse specializing in diabetes. The sessions will be one hour a day with clear and concise information to guarantee the attention and concentration of the participants. This education program offers advanced and centralized training in diabetes care.

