#### 2.4.2. Usual Care

Participants in the control group will receive the usual services offered in the endocrinology and nutrition unit of the university hospital, which include regular visits with a doctor specializing in endocrinology and with a nurse educator and standard Spanish Diabetes Society information pamphlets. Consultation care will be centralized in the pharmacological treatment regimen, dosage and guidelines.

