### 2.7. Ethical Considerations

Upon ethical approval, participants will be recruited during their visits to the endocrinology and nutrition unit of the hospital. The principal investigator will check the eligibility of each potential study candidate. The study will be explained orally to the patient, and a copy of the signed written informed consent document will be offered. All doubts presented by the participant will be resolved, and participants will be able to revoke their consent at any time. Participation will be voluntary, and the data obtained will be completely anonymous for people outside the research team. The researchers on this study obtained the permissions of those responsible for the participating entities and the approval of the corresponding ethics committee.

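### A constant, published block of ten at one hospital with unmaskable arms makes about one allocation in six knowable in advance to anyone who tracks the earlier ones

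*Protocol article*

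**What the plan says.** **Allocation.** Section 2.2 of the protocol article: "Randomization in blocks of 10 will be used (five experimental and five controls) to achieve balance in the randomization procedure". No variation in block size and no strata are mentioned. On concealment, the same section says: "A person unrelated to the research objectives and data collection will prepare the sealed envelopes according to the generated randomization list". It does not say who holds or opens the envelopes, or whether recruiters learn earlier results.

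**Setting and recruiters.** Section 2.2 describes a single hospital: "They will be recruited through random sampling at a public hospital in Spain". It also says: "Participants will be recruited during an endocrinology consultation with a medical professional specializing in diabetes". Under section 2.7, "The principal investigator will check the eligibility of each potential study candidate".

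**Arms.** Section 2.4.1: "Participants randomized to the intervention group will receive a structured program of therapeutic education organized over four consecutive days". Section 2.4.2: "Participants in the control group will receive the usual services offered in the endocrinology and nutrition unit of the university hospital". The term open-label does not appear, but a patient or educator cannot be unaware of four days of teaching. The Limitations section offers three safeguards: analysts separate from the educators, educators not told the objectives, and a research nurse who gives the questionnaires. That nurse is not said to be blind to arm.

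**Primary outcome.** The Abstract names patients' knowledge of diet and treatment management. Section 2.5.2 measures knowledge with ten short questions, and the Limitations section calls this questionnaire non-validated.

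**The concern.** In a 5:5 block of known size, the tenth allocation always follows from the first nine, and often one or more before it are settled too. Varying the block size and keeping it undisclosed normally prevents this. Here the size is constant and printed in a public article, and everyone is recruited through one unit, where staff could plausibly notice who attends the sessions.

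A recruiter who knows the next arm can hurry, delay or discourage a particular patient. Some exclusions in section 2.3.2, such as reading and hearing difficulties, need judgement. If more motivated patients were enrolled when education was due next, the arms would differ at entry in a way that favours education on a knowledge test, and no analysis could fully correct that.

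**Working it through.** The article gives no figure for predictability, so there is none to reproduce.

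**Inputs.** Block of 10 split 5:5 and N = 176, both from section 2.2. N serves only as a count: 176 = 17 × 10 + 6, so 17 full blocks and 6 patients of an eighteenth.

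**Assumption.** The recruiter knows the block size, where each block starts, and every earlier allocation in order. This is the worst case.

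**1. Certain allocations per block.** The last k allocations are all certain when they are all to the same arm. With C(10,5) = 252 possible orders, the probability is 2 × C(10−k, 5−k) / 252:

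- k = 1: 252/252 = 100%
- k = 2: 2 × C(8,3) / 252 = 112/252 = 44.4%
- k = 3: 2 × C(7,2) / 252 = 42/252 = 16.7%
- k = 4: 2 × C(6,1) / 252 = 12/252 = 4.8%
- k = 5: 2 × C(5,0) / 252 = 2/252 = 0.8%

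The expected number is the sum: 420/252 = 1.67 of 10, or 16.7%. The closed form 2m/(m+1) with m = 5 gives the same, 10/6.

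**2. Over the trial.** The 17 full blocks give 17 × 1.67 = 28.33. In the last six patients, an allocation is certain only if the first five went to the same arm, which adds 2/252 = 0.01. The total is 28.3 of 176, or 16.1%.

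**3. Best guess.** A recruiter who always names the under-filled arm expects m + (2^(2m)/C(2m,m) − 1)/2 correct guesses per block. With m = 5 this is 5 + (1024/252 − 1)/2 = 6.53 of 10, or 65.3%, against 50% by chance. Over 176 patients, with the incomplete last block, it is about 65.0%.

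**4. Is ten too small?** For fixed blocks of 4, 6 and 8 the certain share is 33%, 25% and 20%. Ten is better than each of these. The weakness is that the size is constant and disclosed.

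**5. Effect of varying the size.** I simulated 2,000 trials of 176 patients with block sizes drawn at random from 6, 8, 10 and 12. The observer was allowed to know this set of sizes, but not which one was in use.

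| Scheme | Certain share | Best-guess rate |
|---|---|---|
| Fixed 10 | 16.2% (exact: 16.1%) | 65.1% |
| Random 6/8/10/12 | 0.9% (about 1.5 of 176) | 65.6% |

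The change almost removes the certain allocations and leaves the guess rate where it was.

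**The case against.** The strongest reply is that the predictability depends on facts the article does not give. It does not say that recruiting doctors receive or count earlier allocations. The recruiting specialist, the nurse who teaches and the research nurse who gives the questionnaires are described by separate roles. Without an ordered tally the guess rate is about 50% and nothing is certain. This stands: the 16% is conditional, and even in the worst case about 5 allocations in 6 cannot be known for sure.

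Concealment is also not absent. Sealed envelopes prepared by an independent person protect every allocation that is not already determined. Ten is a fairly large block, and fixed blocks are a common choice. This stands too, but it does not answer the point: the determined allocations are deduced from the past, not read from an envelope.

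Two stronger readings are tempting, and the documents do not support them.

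- **The gap between 65% and 50% as the harm to be removed.** Permuted blocks of this size allow better-than-chance guessing by anyone who tracks the balance, and the remedy does not reduce it.
- **Baseline taken after the arm is known, so that the adjustment of every outcome is biased.** The Abstract says: "Measurements and evaluations will be conducted at the baseline prior to the intervention and at 1 and 3 months from the intervention". Neither this nor sections 2.1 and 2.5 place baseline before or after the opening of the envelope. A condensed article may leave that order to the full protocol, so silence here is not an error. Section 2.6 names no covariate for the analysis of covariance, and the sensor measures are device records rather than patient answers.

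**Conclusion.** The point holds in a limited form. The article commits to a constant, published 5:5 block of ten at one hospital, with arms that cannot be masked. If recruiting staff know the earlier allocations in order, about 28 of 176 (16%) are certain before enrolment despite the sealed envelopes.

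This rests on two things the article does not state. The first, that the trial is effectively open-label, follows safely from the arms. The second, that staff track allocations, is plausible in one unit but not shown. The calculation measures the opportunity for selective enrolment. It does not show that any took place, and it puts no figure on bias in the knowledge score. A change is worthwhile because it is cheap and the primary outcome is a non-validated test.

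**What to change.** For the remaining allocations, generate a new list in permuted blocks of randomly varying size, for example 6, 8, 10 and 12. Only the independent person who prepares the envelopes should know the sizes. Section 2.2 should say that block sizes vary and are not disclosed to recruiting staff, without listing them.

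The cost is a regenerated list and a small text amendment. No patients or visits are added, and allocations already made are unaffected. The downside is a final imbalance of a few patients if recruitment stops inside a block. Within an unfinished block of 12 the largest possible difference is 6 (6 against 0). The present scheme is not free of this, because its last 6 patients could split 5 to 1, a difference of 4.

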### 2.6. Data Analysis

All data obtained will be analyzed using the statistical tool IBM SPSS 24.0. Baseline data will be compared between groups using chi-square analysis or independent *t*-test. Parametric statistical tests will be used after checking the normal distribution of the sample. Repeated-measures analysis of covariance will be performed, and the interaction effects on each continuous outcome will be calculated. The chi-square test or Fisher’s exact test will be used to determine the differences in glycemic control and self-care between the two groups. Logistic regressions will be performed to determine the influence of the independent variables on the selected dependent variable. The level of statistical significance will be set at a p value of less than or equal to 0.05. 

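### The 176 participants for 95% power match a one-sided t-test, while the planned tests are non-directional; on the stated inputs a two-sided comparison at one time point has 91% power

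*Protocol article*

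**What the plan says.** Section 2.2 of the protocol article takes a medium effect size and ties the sample size to a named analysis: "Given the medium effect size (0.5), a repeated-measures analysis of covariance will be performed to test for differences between the two groups". It then concludes that "approximately 176 participants will be required to achieve a 95% power at a 5% level of significance". Allocation is 1:1 ("Randomization in blocks of 10 will be used (five experimental and five controls"), so 176 means 88 per arm. Section 2.1 has three measurement times: assessments "will be conducted at the baseline and at 1 and 3 months from the intervention".

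Section 2.6 sets the criterion: "The level of statistical significance will be set at a p value of less than or equal to 0.05". It describes the main analysis as follows: "Repeated-measures analysis of covariance will be performed, and the interaction effects on each continuous outcome will be calculated". Chi-square or Fisher tests and logistic regression are also planned. The article states neither one-sided nor two-sided testing. It gives no within-patient correlation, and no allowance for loss beside the 176.

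**The concern.** The sample size is a figure that the article itself asserts, so it should follow from the inputs printed next to it. The F and chi-square tests in section 2.6 are non-directional, and no one-sided hypothesis appears anywhere. Judging them at 0.05 is therefore, by inference, a two-sided 5% rule. If 176 came from a one-sided calculation, the stated 95% belongs to a different test from the one to be run.

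What is at stake is how a null result would be read. A claim of 95% power tells the reader that a true effect of 0.5 would be missed 5% of the time. For the simplest two-sided comparison the figure at 176 is 9%, before any loss to follow-up.

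**Working it through.** **Inputs.** Effect 0.5, power 0.95, level 0.05, N = 176 (section 2.2; level repeated in section 2.6); 1:1 allocation (section 2.2); three measurements (section 2.1). I read 0.5 as a standardised mean difference d, because the article calls it medium; for two groups this equals f = 0.25. Correlations and loss rates below are my assumptions.

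**1. Reproducing 176.** Two-sample t-test, n per arm, df = 2n − 2, non-centrality δ = d·√(n/2).
- n = 88: δ = 0.5 × √44 = 3.317. One-sided critical value 1.654, power 0.951.
- n = 87: power 0.949.

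So 88 per arm, 176 in total, is exactly the one-sided answer.

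**2. Same inputs, two-sided.**
- n = 88: critical value 1.974, power 0.910.
- n = 104: 0.948. n = 105: 0.950. So 95% needs 210 in total.
- Assumed loss of 10%, 15% or 20% (79, 74 or 70 per arm): 0.878, 0.856, 0.836.

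**3. One follow-up, baseline as covariate.** Non-centrality λ = (N·d²/4)/(1 − ρ²) = 11/(1 − ρ²), F on 1 and 173 df.

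| ρ (baseline to follow-up) | Power at 176 |
|---|---|
| 0 | 0.910 |
| 0.3 | 0.933 |
| 0.4 | 0.949 |
| 0.41 | 0.951 |
| 0.5 | 0.968 |

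**4. Mean of both follow-ups, baseline as covariate, d = 0.5 at both visits.** λ = 11/v, with v = (1 + ρ_F)/2 − ρ_B². Here ρ_F is the correlation between the follow-ups and ρ_B that from baseline to each follow-up.
- Common ρ: v is largest at ρ = 0.25, where v = 0.5625 and λ = 19.56, so power is at least 0.993.
- ρ_F = 0.8, ρ_B = 0.3: v = 0.81, power 0.956.
- ρ_F = 0.8, ρ_B = 0.2: v = 0.86, power 0.945.

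**5. Group-by-time interaction over three times.** Take group differences of 0, 0.5 and 0.5, and a common ρ. The differences average 1/3, so the squared deviations sum to 1/9 + 1/36 + 1/36 = 1/6. Then λ = (176/4)(1/6)/(1 − ρ) = 7.33/(1 − ρ), F on 2 and 348 df.

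| ρ | λ | Power at 176 |
|---|---|---|
| 0.2 | 9.17 | 0.775 |
| 0.5 | 14.67 | 0.937 |
| 0.6 | 18.33 | 0.976 |

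**6. Another two-sided route to 176.** The between-group F test averaged over three measurements has λ = f²·N·m/(1 + (m − 1)ρ). With f = 0.25, m = 3 and ρ = 0.75, λ = 0.0625 × 176 × 3/2.5 = 13.2 and power is 0.951, so 176 also comes out here. But this formula places the 0.5 difference at all three times, including the pre-intervention baseline. With no baseline difference the average effect is two-thirds as large, and power at 176 falls to 0.673 (0.768 at ρ = 0.5).

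**The case against.** The strongest reply is that the article does not power an unadjusted t-test. It names a repeated-measures ANCOVA, which uses the baseline and a second follow-up, and the 91% ignores both. With a common correlation, the mean of the two follow-ups has over 99% power at 176 (step 4), and even one follow-up reaches 95% at ρ of about 0.4. There is also a two-sided formula that returns 176 (step 6), so the one-sided origin is likely but not proven. Sidedness, correlations and loss allowance are details that a condensed article may leave to the full protocol.

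Much of this stands. A reader might infer that the design has only 91% power, that the type II risk is 9%, or that 210 patients are needed. The documents do not support that for the named analysis, because its power depends on correlations and a contrast that are not given. Nor is the absence of a correlation or a loss allowance from an article a fault in itself.

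The reply does not rescue the figure, however. The result in step 4 holds for one contrast, and it drops to 94.5% when the follow-ups correlate strongly and the baseline weakly. Section 2.6 points to interaction effects, and that test is below 95% at ρ of 0.5 or less (step 5). The route in step 6 counts an effect before the intervention. Of the calculations tried here, only the one-sided t-test returns 176 from the printed inputs alone.

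**Conclusion.** The point holds in a limited form. The 176 is the exact one-sided two-sample t-test result, while the planned tests are non-directional. On the stated inputs alone, a two-sided comparison at one time point has 91% power instead of 95%, and about 86% under an assumed 15% loss.

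For the repeated-measures ANCOVA the true figure may lie on either side of 95%: about 94% to over 99% for the mean of both follow-ups, and about 78%, 94% and 98% for the interaction at ρ = 0.2, 0.5 and 0.6. The 95% is therefore unsupported as stated, not disproved.

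This rests on reading 0.5 as d, on inferring two-sided testing from the F and chi-square tests, and, for the repeated-measures figures, on d = 0.5 at both follow-ups. Severity is moderate: even 91% is good power, and neither the design nor the recruitment target has to change.

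**What to change.** Keep 176 and replace the sentence in section 2.2 with a two-sided statement, in one of two forms:

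- *176 analysed participants (88 per arm) give 91% power for d = 0.5 at two-sided alpha 0.05 in an unadjusted comparison at one follow-up, and about 86% if 15% are lost.*
- Keep 95%, but only together with the specific ANCOVA contrast (single follow-up, mean of both follow-ups, or group-by-time interaction) and the within-patient correlation that deliver it two-sided.

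The first form is a conservative reference figure if the primary contrast is an adjusted comparison of follow-up values, and should be labelled as unadjusted. It is not a lower bound for the interaction test, which can fall below it. The second form needs a source for the correlation. Either way the cost is one sentence, no extra patients, and in the first form a slightly less favourable stated power.
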